#### ◦ Economic evaluation

MOSAIC involved a significant investment of economic resources (time and money) from health professionals, training providers, mentors and women at risk. Participation in MOSAIC might also lead to a change in use of health care and other services that could increase or reduce the total provision of services to women at risk. In recognition of this investment, MOSAIC included economic evaluation to assess the outcomes achieved relative to the cost of resources required to achieve them. With multiple outcomes of interest, the economic evaluation took the form of a cost-consequences analysis where the difference in costs experienced between the two trial arms is compared to the difference in all outcomes included in outcome evaluation.

### Data analysis and reporting

The primary analysis will be by 'intention to treat' (allocation): first, descriptive statistics of the characteristics of the Intervention and Comparison groups at recruitment have been calculated to check that cluster randomisation resulted in similar groups (see Tables 1 &2 below). With the main analysis, a comparison of the primary outcomes pre – and post intervention is to be undertaken. These are depression (mean EPDS score and the proportion with a 'probable depression' score (>12)), the proportion experiencing no (0) low levels (CAS 3–6) or high levels of abuse (CAS → 7) on the Composite Abuse Scale), the mean score on the short form of the Parenting Stress Index and the mean subscale score on parent-child interaction. All analyses will be carried out using STATA 10 [48], adjusting for clustering by practice/nurse team. As there is an imbalance in one major prognostic factors despite randomisation, multivariable logistic regression will be used to take this into account. Although numbers of participating Vietnamese women will be too few to undertake adequately powered sub-group analyses, process and outcome data will provide useful information about the acceptability of the intervention in this ethnic community and identify any major trend towards differential outcomes in this group.

**Table 1 T1:** Socio-demographic characteristics of participants in both arms of the MOSAIC study

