### Sample size considerations

With 80% power and 95% confidence, MOSAIC aimed to detect a difference of 16% in abuse or depression a year after recruitment. This was originally estimated to require 165 women in each trial arm with individual randomisation. This reduction was thought to be attainable from a level of any prevalence value for either IPV or depression between 30% and 70% in the control group of women already identified by their GPs as abused or at risk. With cluster randomisation, assuming an intra-class correlation of 0.02 (previously found in a GP partner violence study [18]), the sample size required increased to 190 in each arm. Given the mobility of this vulnerable, sometimes fearful population an expected attrition and loss to follow up of as much as 45% could be expected, requiring 350 to be recruited in each arm. Piloting data indicated that 40 weeks would be required for referral and recruitment of this required number of participants.

By May 2007 (well beyond the 40 week period), both referral and recruitment had been slower than expected and the ratio of intervention to comparison for both those referred and recruited was approximately 2:1. At this stage 131 women in the intervention arm and 71 women in the comparison arm had been referred and of these 63% had been recruited. It was decided to extend the recruitment period for another 7 months, and include one additional MCH nurse team in each arm of the trial.

The estimated sample size was recalculated and we then estimated that, for simple random sampling, with 118 in the intervention arm and 64 in the comparison arm, the study would have 80% power and 95% confidence of being able to detect a difference between arms of 22% for IPV, 18% for depression and two units in the mental component score (MCS) of the SF36. Allowing for the overall 37% attrition rate seen to that time and the 10% inflation factor for the cluster sampling, we hoped to achieve total referrals of 206 women (+75) in the intervention arm and 112 (+41) in the comparison arm to be referred in the extra time period.

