### Sample description

Table 1 below describes participant characteristics in both arms of the trial. There are very few differences in the socio-economic profiles of participants in the two arms of the study. A slightly higher proportion of women in the comparison arm have less than 12 years of education. However, both groups have a high percentage of women with indicators of disadvantage. Over 70% in both arms have a health care card (i.e. government coverage of health care costs for those with inadequate income), over half are dependent on a pension or benefit (e.g. single-parent support), over half have only completed either apprenticeship level, year 12 education or below and while most are Australian citizens, over a third are born overseas. Very few Vietnamese women (n = 4) were referred in the comparison arm.

Table 2 describes the distribution of scores at baseline on primary outcome measures, namely levels of abuse and depression. GPs and nurses identified abused and depressed women to MOSAIC, but at very low levels over the extended two year period. The proportion of women abused (CAS ≥ 7) is comparable between arms (≥ 80%), and the proportion of women abused among those victimised in the previous 12 months (the majority) is equal in both arms (95%). The proportion of women depressed (EPDS ≥ 13) is higher in the intervention arm than in the comparison arm, with a difference in mean baseline EPDS score (15.4 in the intervention arm, 13.0 in the comparison arm).

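### The main analysis is worded as a pre-post comparison without the between-arm contrast at 12 months, and the only model named for the baseline imbalance cannot serve mean EPDS or the PSI means

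*Protocol article*

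**What the plan says.** Under Data analysis and reporting, the protocol article sets the grouping: "The primary analysis will be by 'intention to treat' (allocation"). It then describes the main analysis: "With the main analysis, a comparison of the primary outcomes pre – and post intervention is to be undertaken". The primary outcomes listed there include "depression (mean EPDS score and the proportion with a 'probable depression' score (>12")), abuse as none, low or high on the CAS, the mean PSI short-form score and the mean parent-child interaction subscale. All analyses are to be done "adjusting for clustering by practice/nurse team". On imbalance the section says: "As there is an imbalance in one major prognostic factors despite randomisation, multivariable logistic regression will be used to take this into account". The factor is not named.

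Sample description reports a "difference in mean baseline EPDS score (15.4 in the intervention arm, 13.0 in the comparison arm"), the only primary measure it describes as differing between arms. Sample size considerations frames the target as a contrast between arms: the recalculated size is for "being able to detect a difference between arms of 22% for IPV", with 18% for depression.

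**The concern.** The sample size answers whether the arms differ a year after recruitment. The analysis sentence speaks of before and after, and does not say how the arms are compared. Analysis by allocation fixes who belongs to which arm. It does not fix whether the comparison uses 12-month scores, change from baseline, or 12-month scores adjusted for baseline.

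With balanced arms, all three estimate the same quantity. Here the mentored arm starts 2.4 EPDS points higher, so with no effect the three have different expectations, and the two unadjusted ones err in opposite directions. The one stated repair, logistic regression, applies to proportions. Mean EPDS, mean PSI-SF and the mean parent-child subscale are left without a stated adjusted comparison. The imbalance is already published and the Blinding section says research staff knew participants' status, so the choice should be fixed before the 12-month outcomes are analysed.

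**Working it through.** **1. Which contrast is the trial sized for?** Inputs from Sample size considerations: 80% power, 95% confidence (two-sided 5% assumed), a 16-point difference, control prevalence 30% to 70%. The two-proportion formula with continuity correction has its worst case near 60% v 44%:

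- uncorrected n = [1.96√(2 × 0.52 × 0.48) + 0.842√(0.60 × 0.40 + 0.44 × 0.56)]² / 0.16² = 151.9
- corrected n = (151.9/4) × [1 + √(1 + 4/(151.9 × 0.16))]² = 164.1, so 165 per arm, as stated.

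The stated size is therefore that of a comparison of two arms at one time point.

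**2. Baseline gaps.**

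- Mean EPDS: 15.4 − 13.0 = 2.4.
- EPDS ≥ 13 (Table 2, non-missing): 81/113 = 71.7% v 33/59 = 55.9%, a gap of 15.7 points before rounding.
- CAS ≥ 7: 82% v 80% of all women (93/113 = 82% v 48/56 = 86% of those with a score). There is no comparable gap.
- PSI: no baseline values are given.

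**3. Mean EPDS with no treatment effect.** Assume equal SDs, a baseline to 12-month correlation r (not in the article) and a chance gap. The expected difference, mentored minus comparison, is:

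| Analysis | Formula | r = 0.4 | r = 0.5 | r = 0.6 |
|---|---|---|---|---|
| Unadjusted change | −2.4(1 − r) | −1.44 | −1.20 | −0.96 |
| Unadjusted 12-month score | +2.4r | +0.96 | +1.20 | +1.44 |
| 12-month score adjusted for baseline | 0 | 0 | 0 | 0 |

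Negative favours mentoring. Over r from 0.3 to 0.7 the change-score figure runs from −1.68 to −0.72.

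**4. False-positive rate of the change-score test, given the 2.4-point gap.** Inputs: 114 and 60 women (Table 1); retention 55% (the article's 45% attrition) to 80% (assumed); SD 5-6 (assumed); variance inflation 1.1 (the article's 10% for clustering). Let k = √(1/n₁ + 1/n₀) × √1.1.

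- The test uses SE = SD × √(2(1 − r)) × k.
- Given the baseline values, the estimate varies with SD × √(1 − r²) × k, which is smaller.
- Upper end (r = 0.4, SD 5, 80% retained: 91.2 and 48 women): k = 0.187, SE = 1.024, conditional SD = 0.857. P = 1 − Φ[(1.96 × 1.024 − 1.44)/0.857] = 1 − Φ(0.66) = 0.25.
- Lower end (r = 0.6, SD 6, 55% retained: 62.7 and 33 women): k = 0.226, SE = 1.210, conditional SD = 1.083. P = 1 − Φ[(1.96 × 1.210 − 0.96)/1.083] = 1 − Φ(1.30) = 0.10.

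The other combinations lie between, so the range is about 10-25% against a nominal 5%.

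**5. Proportion depressed.** Suppose the 12-month rate is a in women depressed at entry and b in the others, the same in both arms. The mentored arm then shows a larger unadjusted fall by 15.7 × (1 − (a − b)) points. For a = 0.7, b = 0.2 that is 7.9; for a = 0.5, b = 0.3 it is 12.6 (rates assumed). A logistic model with baseline depression as covariate deals with this, if baseline depression is the factor meant.

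**The case against.** The strongest reply is that the sentence is loose but its setting is clear. Analysis is by allocation, the two groups are named, the sample size is for a difference between arms, and an imbalance between arms needs adjustment only if the arms are compared. A reader might infer that the plan is to run separate before-and-after tests within each arm and discard the control group. The documents do not support that: the same paragraph and the sample size section point to a between-arm comparison, and the wording may mean only that baseline and 12-month measurements are both used. This part of the reply stands.

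A reader might also infer that the trial's result as a whole is biased towards mentoring. That goes too far, for three reasons. The aim and power for depression concern the proportion depressed, for which a logistic model is planned. High abuse is balanced at entry. And the direction assumes a chance gap: clusters were randomised before women were referred, providers were not blinded, and the Discussion reports reluctance to refer in the comparison arm. If the gap reflects who was referred, its direction of bias is not certain and baseline adjustment may not remove all of it.

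Finally, an article condenses a plan, and the exact linear model could be left to a fuller document. That would hold if the article were silent. Instead it states a main comparison that omits the contrast, and a remedy for imbalance whose type does not fit three of its own primary measures. What remains is a text to correct, not proof of a wrong analysis.

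**Conclusion.** The point holds as an ambiguity with a material consequence for one outcome. The stated main analysis does not write out the between-arm contrast at 12 months, the imbalanced factor is unnamed, and logistic regression cannot adjust mean EPDS, mean PSI-SF or the mean parent-child subscale.

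For mean EPDS, the unadjusted analyses that the wording leaves open differ in expectation by the full 2.4 points: 1.0 to 1.4 points towards mentoring for change scores, 1.0 to 1.4 against it for 12-month scores. The change-score test would have a false-positive rate of about 10-25%. These figures rest on an assumed correlation of 0.4-0.6, SD 5-6, 55-80% retained, and a gap due to chance. None of them shows that the trial will use change scores. No such bias is shown for CAS ≥ 7 or, for want of baseline data in the article, for the PSI measures.

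**What to change.** Replace the sentence on the main analysis with wording such as: *The main analysis compares the two arms at 12 months by allocation, allowing for clustering by practice or nurse team. Each outcome is adjusted for its own baseline value: a linear model for the EPDS and PSI means, a logistic model for EPDS > 12, and an ordinal or logistic model for the existing none, low and high CAS categories. Pre-post figures within each arm are descriptive only.*

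Name baseline EPDS as the imbalanced prognostic factor, if that is what is meant. Add a line acknowledging that adjustment may not remove all bias if referral differed between arms.

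The cost is a few sentences. The Abstract describes baseline and 12-month surveys with these instruments, so no new data are needed, and the outcome definitions stay as they are.

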### MOSAIC Aims

The primary aims of the trial were:

• to reduce partner violence by 16% among women pregnant and/or with children under five whom GPs or MCH nurses identify as abused or at risk;

• to reduce depression by 16% in women pregnant and/or with children under five whom GPs or MCH nurses identify as abused or at risk; and

• to strengthen the general health and wellbeing and mother-child bonding of abused or at-risk women.

The secondary aims were:

• to strengthen infrastructure support for primary care management of partner violence, by enhancing effective inter-sectoral collaboration between general practice and community-based family violence networks; and

• to enhance primary care case management of family members living with partner violence.

The major hypothesis tested in MOSAIC was that mentor mother support would reduce both partner abuse and depression and the hypothesised pathway for this to occur was the following:

• that by reducing isolation, providing links to community resources and using strength-based support, sustained help from mentor mothers to women who are pregnant and/or have children under five referred by their primary care provider will encourage women to take actions to increase their safety; and

• that any reduction of abuse, together with continued non-professional mentor support, will reduce the level of depression and enhance women's general health and mother-child bonding.

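### Mean EPDS is a primary depression outcome, but the only adjustment named for the baseline imbalance is logistic regression, and depression power is given only for a proportion

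*Protocol article*

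**What the plan says.** **Outcomes.** The Data analysis and reporting section of the protocol article lists, among the primary outcomes, "depression (mean EPDS score and the proportion with a 'probable depression' score (>12"). Both forms are primary, and no order is set between them. All analyses are to allow for clustering by practice or nurse team.

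**Adjustment.** The same section states: "As there is an imbalance in one major prognostic factors despite randomisation, multivariable logistic regression will be used to take this into account". It names no other adjusted model and does not name the factor. The Sample description section and Table 2 point to depression: mean EPDS is 15.4 in the intervention arm and 13.0 in the comparison arm, and 81 of 114 (71%) v 33 of 60 (55%) score 13 or more.

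**Aim and size.** The aim is "to reduce depression by 16% in women pregnant and/or with children under five". The Sample size considerations section says: "With 80% power and 95% confidence, MOSAIC aimed to detect a difference of 16% in abuse or depression a year after recruitment". It takes the control rate to be "any prevalence value for either IPV or depression between 30% and 70% in the control group". The recalculation, for 118 v 64 women under simple random sampling, claims 80% power to "detect a difference between arms of 22% for IPV, 18% for depression and two units in the mental component score". It gives no control rate for the 18 points and no detectable difference or SD for mean EPDS.

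**The concern.** Once the arms differ in baseline depression, the adjusted result is the one readers will trust. The article commits to an adjustment method, and that method cannot be fitted to a mean score. Taken as written, the more informative form of the outcome has no stated adjusted analysis, and the form that has one is the less efficient.

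Two things are at stake. First, if 12-month mean EPDS is compared without adjustment, the baseline difference carries forward and hides part of any benefit. Second, if the adjusted depression result comes only from the proportion above 12, it has clearly less power than the same data can give. The trial recruited 114 and 60 women before any loss to follow-up, so it has little power to spare.

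**Working it through.** **1. The plan's own figures.** Two proportions, 60% v 44%, 80% power, two-sided 5%, with continuity correction: 164.1, rounded up to 165 per arm, as stated ("This was originally estimated to require 165 women in each trial arm with individual randomisation"). The recalculated sizes also follow: 206 × 0.63 / 1.1 = 118 and 112 × 0.63 / 1.1 = 64.

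**2. Power of the two forms at 118 v 64.** Assumption: 12-month EPDS is normal with equal SDs and the intervention shifts it. Let pC and pT be the proportions above the cut.

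- Standardised shift: d = z(pC) − z(pT). For 55% v 37%, d = 0.126 + 0.332 = 0.458.
- Score: power = Φ(d / √(1/118 + 1/64) − 1.96), where the root is 0.1552.
- Proportion: power = Φ((0.18 − 1.96 × SE0) / SE1), with SE0 pooled and SE1 unpooled. For 55% v 37%, SE0 = 0.0769 and SE1 = 0.0764, so power is 65%.

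| Control rate | Proportion >12 | Mean score | Gap (points) |
|---|---|---|---|
| 30% | 83.2% | 98.7% | 15.5 |
| 40% | 72.4% | 91.7% | 19.3 |
| 50% | 66.4% | 85.4% | 19.0 |
| 55% | 64.9% | 83.8% | 18.9 |
| 60% | 64.3% | 83.5% | 19.2 |
| 70% | 65.8% | 86.3% | 20.5 |

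Simulated whole-number EPDS scores from 0 to 30, with SD 5 or 6, give gaps of 14 to 20 points. With the 114 and 60 women recruited and none lost, the 55% row becomes 62.6% v 81.8%. All these tests are unadjusted. Adjusting the score for baseline EPDS at an assumed correlation of 0.5 multiplies its variance by 1 − 0.5² = 0.75 and raises its power in the 55% row (118 v 64) to about 92%. The gain from adjusting the logistic model was not computed.

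**3. Bias in an unadjusted mean.** The baseline gap is 15.4 − 13.0 = 2.4 points. With correlation ρ and equal SDs at both times, ρ × 2.4 is expected to persist at 12 months. Assume SD 5. For the intervention arm, a normal score with mean 15.4 and 81/113 at 13 or more implies about 5.1. The comparison arm implies about 3.4, but poorly, because its mean lies close to the cut.

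- True effect for 55% v 37%: 0.458 × 5 = 2.3 points.
- Carried forward at ρ = 0.5: 1.2 points, or 0.24 SD.
- Shift left to detect: 0.458 − 0.24 = 0.218.
- Power: Φ(0.218 / 0.1552 − 1.96) = 29%, against 84% without imbalance.
- At SD 5, power is 52% for ρ = 0.3 and 12% for ρ = 0.7. At ρ = 0.5, it is 17% for SD 4 and 38% for SD 6.

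**4. The 18-point figure.** On the cut at 118 v 64, an 18-point reduction has 80% power at a control rate near 33%, the only such point between 30% and 70%. At 55%, the comparison arm's baseline rate, power is about 65% and the difference detectable with 80% power is about 21 points.

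**The case against.** The strongest reply is that mean EPDS is already a primary outcome and is listed first. This stands. A reader might infer that the depression question as a whole rests on the cut and so gives up 15 to 20 points of power. The documents do not support that: the score is to be analysed, and the loss falls on the binary form and on the one adjusted analysis that is named. Nor does the aim itself name a cut; the link comes from the sample-size section's use of prevalence.

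A second reply is that a condensed article may leave the linear model to a fuller plan, and that mean parenting-stress scores are also primary, so logistic regression cannot have been meant for everything. This is fair as to intent. But the article does choose a method to deal with the imbalance, and that method does not fit half of the depression outcome. The section also speaks of comparing outcomes before and after intervention. If that means comparing changes, subtracting the full 2.4 points where only 1.2 is expected to persist would err by 1.2 points the other way.

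A third reply is that the power gap depends on assumptions. It does. At the original 165 per arm with a 16-point difference it is only about 6 to 12.5 points. It would also be wrong to argue that baseline means near the cut make the loss worse: for a small shift in a normal score, a central cut loses least.

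**Conclusion.** The point holds in a limited form. The only adjustment stated cannot be applied to mean EPDS, although baseline EPDS differs by 2.4 points between arms, and depression power is stated only for a proportion.

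An unadjusted comparison of 12-month means would be biased against the intervention by about 1.2 points, roughly half of a 2.3-point effect, if the SD is 5 and the correlation 0.5. Neither figure is in the documents. The binary form has about 15 to 20 points less power than the score at 118 v 64 for an 18-point difference, given a normal shift with equal SDs; clustering and loss to follow-up lower power on both scales. That baseline depression is the unnamed prognostic factor is an inference from Table 2, though a strong one.

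The documents do not show that mean EPDS will go unadjusted, or that a real shift in it will be reported as no effect. They show that the stated plan does not prevent this.

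**What to change.** In Data analysis and reporting:

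- State that 12-month EPDS score is analysed by linear regression on arm and baseline EPDS, with the planned allowance for clustering.
- Report this adjusted mean difference as the main estimate for the mean-EPDS primary outcome.
- Keep the proportion above 12 beside it, from logistic regression also adjusted for baseline EPDS.
- Name the imbalanced factor.

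In Sample size considerations:

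- Add the detectable difference in mean EPDS with its assumed SD. At 118 v 64 and 80% power it is (1.96 + 0.84) × 0.1552 = 0.43 SD unadjusted, about 2.2 points at SD 5 (1.7 to 2.6 for SD 4 to 6). With correlation 0.5 and adjustment it is about 1.9 points at SD 5.
- State the control rate behind the 18-point figure.

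No new data are needed, since baseline EPDS is already collected and the analysis is described as still to be done. The cost is slightly more analysis work and, if the control rate is nearer 55% than 33%, a less favourable stated power for the proportion.

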### Recruitment of the clusters: GP practices and maternal and child health teams

Prior to study commencement, support for MOSAIC was obtained from the five General Practice Divisions in the planned catchment area for the study, and permission granted to contact GP practices in the region. General practitioners (GPs) were invited from practices included in the Maternity Affiliate Shared Care List for the Victorian Department of Human Services North West Region, and GPs who were members of the five participating Divisions of General Practice (including all Vietnamese GPs in the region) were also sent letters of invitation. Vietnamese GPs were approached in person by a Vietnamese project officer and invited to participate. MCH nurse teams located in six local government areas in North West Melbourne were informed about MOSAIC and invited to participate.

Formal written invitations included information about: the rationale and design of MOSAIC; the requirement for participation in six hours of professional development addressing IPV identification and management; a commitment to invite and refer women to the study for a required period of time; acceptance of the process of randomisation; a copy of the Memorandum of Understanding regarding participation; and contact details for further information about the trial.

24 GP practices (27 GPs) and six (later increased to eight) MCH teams agreed to participate by returning a signed copy of the Memorandum of Understanding.

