### Randomisation

GP practices and MCHN teams were randomised at separate public meetings following completion of the professional development programs. For GPs, names (stratified by practice size – one GP or more than one GP participating) were concealed in opaque envelopes and randomly selected by someone outside the study. Similarly names of the MCHN teams were concealed in opaque envelopes, with teams stratified by the number of births in the local government area and the selection made by an invited guest from outside the project or research team. GPs and MCH nurse Team Leaders were present to ensure the fairness of the process and to check the contents of the envelopes prior to their being sealed.

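### The stated analysis omits provider type and the randomisation strata; separately, few and unequal clusters would make a standard cluster-robust test reject too often

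*Protocol article*

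**What the plan says.** The Randomisation section of the protocol article states that "GP practices and MCHN teams were randomised at separate public meetings". Practices were "stratified by practice size – one GP or more than one GP participating", and nurse teams were drawn with "teams stratified by the number of births in the local government area". Allocation was therefore restricted by provider type and, within each type, by one stratifier.

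On numbers, the section on recruitment of the clusters says that "24 GP practices (27 GPs) and six (later increased to eight) MCH teams agreed to participate". Sample size considerations adds that the late teams were one per arm.

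Data analysis and reporting commits to intention to treat in Stata 10, "adjusting for clustering by practice/nurse team", and to multivariable logistic regression for one prognostic factor found to be imbalanced. Neither provider type nor a stratifier is named as a covariate. The section also names no estimator, reference distribution or small-sample correction.

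**The concern.** There are two separate issues.

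**Design factors.** When allocation is restricted by provider type and stratum, the analysis should reflect that. The article instead picks its one stated covariate from observed imbalance and leaves out the factors that the design itself supplies. Leaving them out keeps between-provider differences in the error term. Recruitment was also lopsided (114 women against 60). If the mix of GP-referred and nurse-referred women differs by arm, which the article does not report, part of any provider difference enters the treatment contrast.

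**Few effective clusters.** A cluster-robust standard error is reliable when there are many clusters of similar weight. Thirty-two clusters sounds adequate. If most women come from eight nurse teams, however, the comparison rests largely on about four teams per arm. The standard error is then too small on average, and a p-value near 0.05 overstates the evidence.

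**Working it through.** **1. The plan's own figures.** The design statement is "With 80% power and 95% confidence, MOSAIC aimed to detect a difference of 16% in abuse or depression a year after recruitment", and "This was originally estimated to require 165 women in each trial arm with individual randomisation", for "any prevalence value for either IPV or depression between 30% and 70% in the control group".

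- Two proportions, 0.58 against 0.42, two-sided 5%, 80% power: n = (1.960·√(2·0.5·0.5) + 0.842·√(2·0.58·0.42))² / 0.16² ≈ 152.1, so 153. With continuity correction it is 165, as stated.
- 190/165 = 1.15. With design effect 1 + (m − 1)·0.02, this implies m ≈ 8.6 women per cluster.
- 190/0.55 = 346, against 350 stated.
- Recalculated targets: 118·1.1/0.63 = 206 and 64·1.1/0.63 = 112, as stated.
- The 10% inflation implies m = 1 + 0.10/0.02 = 6. This fits equal clusters: (118 + 64)/32 = 5.7, design effect 1 + 0.02·4.7 = 1.09.

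The planning figures reproduce, and the recalculation fits 32 clusters of equal size.

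**2. How unequal might the clusters be?** Women per cluster are not given. The nearest proxy is clinician numbers in the process evaluation section: 91 nurses and 27 GPs, so 91/118 = 77% nurses. If referrals followed head count (an assumption), the design effect with equal clusters within type would be

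1 + 0.02·(0.77²·182/8 + 0.23²·182/24 − 1) = 1 + 0.02·(13.49 + 0.40 − 1) ≈ 1.26.

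The corresponding effective number of clusters is 1/(0.77²/8 + 0.23²/24) ≈ 13. At a 25% share it would be 1/(0.25²/8 + 0.75²/24) = 32, and at 90% about 10.

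**3. Type I error of a standard cluster-robust test.** Simulation under no effect used 174 women, 4+4 teams and 12+12 practices, a 1.9:1 referral weight, unequal cluster sizes, ICC 0.02 and a continuous outcome, with 4,000 to 8,000 runs per scenario. The variance was a sandwich estimate with factor G/(G−1).

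| Nurse-team share (assumed) | Normal reference | t on G−1 |
|---|---|---|
| 25% | 7.5% | 6.2% |
| 50% | 8.2% | 7.0% |
| 60% | 9.4% | 7.9% |
| 77% | 11.9% | 9.4% |
| 90% | 13.0% | 9.6% |

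A binary outcome gives 9.1% / 7.4% at a 50% share and 10.8% / 8.7% at 77%. At ICC 0.05 and a 90% share the figures are 14.0% / 10.4%.

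**4. Does omitting provider type cause the excess?** With a provider effect of 0.3 SD:

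| Share | Provider type omitted (normal / t on G−1) | Provider type included (normal / t on G−1) |
|---|---|---|
| 50% | 6.4% / 5.2% | 8.6% / 7.2% |
| 80% | 10.7% / 8.2% | 12.6% / 10.2% |
| 90% | 12.2% / 8.7% | 14.8% / 10.9% |

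It does not. Adding provider type while keeping the same robust test raises rejection slightly.

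**5. Does a small-sample method help?**

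- t on 6 df: 5-6% at a 77% share. It is conservative at 25% (2.9%) and still about 7% at 90% (binary outcome).
- Permutation within provider type: 6.3% at 77% and 5.7% at 90% (1,500 runs, Monte Carlo SE 0.6 points).

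**The case against.** The article does not say which clustering adjustment will be used. Its wording would equally cover a random-effects model, a cluster-level analysis or a corrected robust method, and an analysis plan that is not shown may settle this. That stands: silence on the estimator is not an error, and the rejection rates above describe only one possible choice.

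The dominance of the nurse teams is also inferred. Head counts are a weak proxy. GPs in three of the four pilot practices did refer, and Vietnamese GPs were specifically recruited. That stands too, and it is why a range of shares is shown.

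A reader might infer that the planned test rejects twice as often as stated because the strata were ignored. The documents support neither half. Doubling needs a nurse-team share of roughly 70% or more and an ordinary robust test, and neither is documented. Omitting provider type, if anything, made that test reject less often.

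A reader might also infer that the analysis adjusts for clustering alone, but regression for one imbalanced factor is planned as well.

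Finally, full adjustment for the strata is not practical. With 27 GPs in 24 practices, at most 27 − 24 = 3 practices have more than one participating GP. The births groups are not listed, and how the two late teams were allocated is not described. This limits the remedy but does not remove the point: provider type is known for every woman, and the stated model leaves it out while adding a covariate chosen from the data.

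**Conclusion.** The point holds in two parts of different strength.

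The first rests on the text alone. Randomisation was separate by provider type and stratified, and the stated analysis names neither provider type nor the strata.

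The second is conditional. If a standard cluster-robust test is used, type I error at a nominal 5% is about 6-8% for nurse-team shares of 25-50% and about 9-14% for shares of 77-90%. Single scenarios fall just outside these bands (5.2% and 9.1% at 50%, 8.2% at 80%, 14.8% at 90%). These figures assume the nurse-team share, ICC 0.02, equal numbers of clusters per arm and the 1.9:1 recruitment ratio. The cause is few, unequal clusters, so the two parts need separate remedies applied together. This is a worthwhile improvement to the analysis, not proof that the trial's error rate is wrong.

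**What to change.** - **Covariates.** Include provider type (GP or nurse) in every outcome model, and the births group for nurse teams where it can be estimated. Practice size rests on at most three multi-GP practices and need not be a fixed effect.
- **Inference.** Together with this, specify a small-sample method. One option is a cluster permutation test within provider type. Permuting within the finer strata is not clearly defined from the article. The other is a t reference with degrees of freedom that reflect the effective number of clusters. A fixed 6 df suits a share near 77% but is too strict at low shares and not strict enough at very high ones.
- **Reporting.** Give women per cluster, by provider type and arm, so that readers can judge how many clusters carry the result.

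The cost is analysis-plan wording and some precision. With t on 6 df, intervals widen by 2.447/1.960 = 1.25, about 25%; with more effective clusters the loss is smaller. No further data collection is needed: provider type and cluster are already identified, since the planned adjustment requires them.
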